### Health Care Costs

Health care costs will include direct medical costs: outpatient visits, emergency room and hospital admissions, and medicines prescribed during the study period.

### Patient and Family Costs

Patient and family costs will include direct nonmedical costs, such as transport for seeking health care and internet expenditures. In São Paulo, we will assume that for each hospital admission, there will be 2 public transport trips. For those aged over 60, we will add a companion cost (according to Article 16 of the Brazilian Elderly Statute) [25]. In case of attendance at the primary care centers, no transportation cost will be calculated, as we are assuming participants will be attending a local service. In Lima, we will consider the use of 2 public transport trips for all participants. For participants aged over 60, considering the lack of specific regulations, we agreed on including an additional 50% cost for caregiver transportation.

We assumed that the patients already own a smartphone and included only the costs of internet access.

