## Methods

### Study Design

The economic evaluation will follow the Methodological Guidelines for Economic Evaluation Studies of Health Technologies [16] and will be reported according to the Consolidated Health Economic Evaluation Reporting Standards (CHEERS) checklist [17]. The multinational economic evaluations will be fully split analyses (incorporating estimates of both resource use and clinical effectiveness from the same group of patients from individual countries) with a multicountry costing approach (applying unit cost estimates from individual countries to account for resource use in each of those countries) [18]. The within-trial analyses will be conducted using data from the randomized control trials NCT02846662 and NCT03026426, and secondary data on health service costs extracted from governmental public databases. This protocol outlines the methods for a cost-effectiveness analysis and cost-utility analysis alongside the RCTs conducted in Brazil and Peru, respectively.

The proposed economic evaluations will be conducted from both the public health care system perspective (including only health care system costs) and the societal perspective (including health care system costs plus patient and productivity costs).

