### Study Population

All participants in the RCT will be included in the economic evaluations. Participants include patients of the public health care system in Brazil or Peru. Inclusion criteria were adults (age ≥21 years), able to read the screen of a smartphone, receiving treatment for hypertension, diabetes, or both (self-report validated with clinical records), and experiencing symptoms of depression. Symptoms of depression were defined as obtaining a score of 10 or more on the 9-item Patient Health Questionnaire (PHQ-9) [19]. Participants were recruited from 20 primary care units in São Paulo, Brazil, and from 4 primary care centers and 3 outpatient clinics in Lima, Peru.

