### CONEMO Plus Enhanced Usual Care

The intervention group received CONEMO plus enhanced usual care. CONEMO is a low-intensity mHealth intervention aimed at reducing symptoms of depression. It is delivered via a smartphone app, and is minimally supported by a nurse/NA. The CONEMO app delivers 18 brief, automated mini-sessions over a 6-week period, with 3 mini-sessions per week. Each session is completed in less than 10 minutes.

The app content is based on behavioral activation, an evidence-based psychological approach to treat depression. Processed data on app usage were collected automatically and reviewed in real-time by nurses/NAs through a dashboard installed on tablets.

Nurses/NAs met with participants for an initial face-to-face meeting, where participants received a smartphone with the app preinstalled and completed a tutorial on its use. Nurses/NAs made 2 mandatory phone calls to all CONEMO participants at the beginning of the program to troubleshoot any difficulties and enhance motivation for the use of CONEMO. Additional calls were prompted through notifications sent to nurses/NAs when the CONEMO automated system detected nonadherence. Patients could request technical help through the help button on the app. Nurses/NAs received training and were supervised weekly by psychologists through face-to-face meetings or via telephone.

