**Intervention (CONEMO^a^) costs**								
	Staff involved in supervision		Hour of supervision	Cost/hour		LATIN-MH^a^ databases		
	Staff involved in training		Hour of a research assistant	Cost/hour		LATIN-MH databases		
	Transport		Number of trips	Cost/trip		LATIN-MH databases		
	Dashboard and app maintenance		Maintenance charge	Cost/month		LATIN-MH databases		
	Internet package		Monthly package	Cost/month		LATIN-MH databases		
	Office supplies			Cost/month		LATIN-MH databases		
	Infrastructure			Cost/month		LATIN-MH databases		

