**Patient and family costs**								
		Transport	Number of trips	Cost/trip		Average cost for public transport		
		Internet	Monthly package	Cost/month		Average market price		

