### Intervention Costs

Intervention costs include the value of the staff time and transport involved in either supervision or training of the primary care workers that will use CONEMO.

We will assume that the intervention (CONEMO) is operational, and so start-up costs, such as design and development of CONEMO, will be excluded. Therefore, we will include only costs for maintenance of the dashboard and app, internet package costs, and expenditures related to office supplies and infrastructure.

All of the research-related costs associated with trial administration, data collection, and outcome assessment of RCTs will be excluded.

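### The costing assumes patients already own a smartphone, but CONEMO participants were given one, so the measured effect is paired with a cost that leaves the device out

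*Protocol article*

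**What the plan says.** All references are to the protocol article.

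- **Delivery** (CONEMO Plus Enhanced Usual Care): at the initial face-to-face meeting "participants received a smartphone with the app preinstalled and completed a tutorial on its use". No exception is mentioned.
- **Eligibility** (Study Population): candidates had to be "able to read the screen of a smartphone". Owning a phone is not among the criteria.
- **Costing assumption** (Patient and Family Costs): "We assumed that the patients already own a smartphone and included only the costs of internet access".
- **Intervention costs** (Intervention Costs): besides staff time and transport for supervision and training, "we will include only costs for maintenance of the dashboard and app, internet package costs, and expenditures related to office supplies and infrastructure". No handset is listed, and Table 2 has none.
- **Design** (Study Design): the analyses are within-trial and fully split, "incorporating estimates of both resource use and clinical effectiveness from the same group of patients from individual countries".
- **Internet**: Table 2 has an "Internet package" line under intervention costs, priced from the LATIN-MH databases. It has a second monthly internet line under patient and family costs, priced at "Average market price". The text on patient costs also names items "such as transport for seeking health care and internet expenditures".
- **Sensitivity Analyses**: one-way analyses will vary resource quantities, unit costs and QALYs. Handset cost and phone ownership are not named.

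**The concern.** A within-trial ICER divides a cost difference by an effect difference measured in the same patients. Here the numerator and denominator describe different packages. The effect was observed in people who were handed a phone with the app on it. The cost describes people who already had one. Only the intervention arm received the device, so leaving it out lowers the incremental cost and favours CONEMO. If the supplied phone is treated as an intervention cost, the omission affects both the public health care system and the societal perspective.

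The Discussion says a favourable ICER would make a strong case for scale-up. A policymaker would need to know whether that ICER depends on patients bringing their own phones.

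**Working it through.** The article states no handset price, QALY gain or ICER, so there is no figure of its own to reproduce. The first step compares the text; the rest only indicates scale.

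**1. Is the handset anywhere in the cost?** It is not in the Intervention Costs list, not in Table 2 under intervention costs, and not in Table 2 under patient and family costs. Patient and Family Costs says why: ownership is assumed. The general infrastructure line cannot be read as containing a phone that the analysis takes the patient to own already.

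**2. Inputs for scale**

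- From the article: thresholds of $PPP 3210-10,122 per QALY (Brazil) and 1969-7747 (Peru); a 6-week programme, or 42 days.
- Assumed: handset price INT$150-300; straight-line life of 3 years (1095 days); QALY gain 0.01125. From equal baselines and with linear interpolation, that gain equals a utility difference of 0.01125 / (0.125 + 0.25) = 0.03 at both 3 and 6 months.

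**3. Incremental cost the thresholds allow** = threshold × QALY gain

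| | Lower | Upper |
|---|---|---|
| Brazil | 3210 × 0.01125 = INT$36 | 10,122 × 0.01125 = INT$114 |
| Peru | 1969 × 0.01125 = INT$22 | 7747 × 0.01125 = INT$87 |

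**4. Handset cost per participant**

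- Full reuse, each phone charged for 42 days: 150 × 42/1095 = INT$5.8; 300 × 42/1095 = INT$11.5.
- No reuse: INT$150-300.

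**5. Share of the allowed cost**

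- Full reuse, lower thresholds: 5.8/36.1 to 11.5/36.1 = 16-32% (Brazil); 5.8/22.2 to 11.5/22.2 = 26-52% (Peru).
- Full reuse, upper thresholds: 5-10% (Brazil); 7-13% (Peru).
- No reuse: INT$150 already exceeds both upper figures (114 and 87).

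**6. Shift in the ICER** = handset cost / QALY gain. Full reuse: 5.75/0.01125 = 511 to 11.5/0.01125 = 1022 per QALY. No reuse: 150/0.01125 = 13,333 to 300/0.01125 = 26,667 per QALY.

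**7. Dependence on the QALY gain.** The shares scale inversely with it. At 0.02 QALY the allowed costs become INT$64-202 (Brazil) and INT$39-155 (Peru). The full-reuse shares at the lower thresholds fall to 9-18% and 15-29%, and a single-use handset at INT$150 fits just under both upper figures. At 0.005 QALY the allowed costs are only INT$16-51 and INT$10-39.

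**8. Internet lines side by side.** Both are monthly packages. One is an intervention cost from project databases; the other is a patient cost at market price. The societal perspective would add them. The intervention description gives two users of connectivity: participants on their phones, and nurses or nurse assistants watching a dashboard on tablets. The article does not say which line belongs to which user.

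**The case against.** **The assumption is disclosed and has a rationale.** Intervention Costs treats CONEMO as already operational and excludes start-up costs, and the Results section says the findings will help plan implementation. Delivery through patients' own phones is a plausible rollout scenario. This stands. A reader might infer that the own-phone case is wrong and must give way as the primary analysis; the article does not support that. Which case is primary is open to debate. What remains is that the assumption sits beside a within-trial label without any acknowledgement that the trial delivered something else, and Study Limitations does not mention it.

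**The handset might count as a start-up cost, or be reached by the sensitivity analyses.** Neither answer holds. The start-up examples are design and development, whereas a phone handed to each participant scales with enrolment. The parameter list for one-way analyses is open-ended, but varying the quantities and prices of listed items does not add an item that is absent.

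**The two internet lines might be read as double counting.** The article does not show this. Different payers and price sources are what two separate connections, tablets and phones, would look like. Any duplication would affect only the societal perspective and would work against CONEMO, opposite to the handset omission. Only the missing definition can be criticised.

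**The size is uncertain.** This stands. Price, life and QALY gain are all assumed, and the result runs from about INT$6 to INT$300 per participant depending mainly on reuse, which the article does not state. That every participant received a phone is inferred from unqualified wording.

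**Conclusion.** The conflict between the delivery description and the costing assumption is in the text and does not rest on any assumed figure. Its direction is also clear: the incremental cost of the intervention as tested is understated. Its size is not known. Under the stated assumptions, the handset takes a modest to substantial share of the allowed cost if phones are fully reused, and more than all of it if they are not. That range is wide enough for the handset to change the conclusion at the article's thresholds, but it does not show that it would. The internet lines call for a clarification only. Overall this is an inexpensive improvement to a disclosed choice.

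**What to change.** 1. Report the ICER and the acceptability curve, for both perspectives, with the supplied handset included as an intervention cost. Annualise it over a stated life and reuse rate, and state how long each participant held the phone.
2. Show the own-phone case alongside. In Patient and Family Costs and in Sensitivity Analyses, say which of the two describes the intervention as tested and which describes routine rollout.
3. For each internet line in Table 2, state whose connection it covers, who pays and in which perspective it counts, and charge each connection once.

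The cost is some wording, a handset price and reuse record, and one extra run; no new patient data are needed. Table 2 lists no device item, so the article does not confirm that the price is already in the LATIN-MH databases. The ICER with the handset included will be less favourable to CONEMO, by an amount that depends mainly on reuse.

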### Productivity Costs

Productivity costs will include indirect costs related to lost days of work due to morbidity and will be estimated according to the human capital approach [26]. Productivity costs associated with depressive symptoms will be calculated by multiplying the number of hours absent with an average hourly wage in Brazil and Peru.

### Analytic Methods

Mean values of the estimated health outcomes and costs, as well as mean differences between the comparator groups (CONEMO plus enhanced usual care versus enhanced usual care) will be reported. Incremental cost-effectiveness ratios (ICERs) will be calculated as the arithmetic mean difference in cost between CONEMO plus enhanced usual care and enhanced usual care, divided by the arithmetic mean difference in effect. For the cost-effectiveness analysis, the corresponding ICER will be expressed as the incremental costs per at least 50% reduction of PHQ-9 scores. In the cost-utility analysis, the ICER will be expressed as the incremental costs per QALY gained. ICERs will be generated by nonparametric bootstrapping methods using random resamples for every 1000 pairs of outcomes and costs for the intervention and comparator groups to derive 95% CIs [27]. The distribution of mean incremental costs and outcomes shown on cost-effectiveness will be conducted to test the robustness of results.

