**Methods:**

The economic evaluation uses a within-trial analysis to evaluate the incremental costs and health outcomes of CONEMO plus enhanced usual care in comparison with enhanced usual care from public health care system and societal perspectives. Participants are patients of the public health care services for hypertension, diabetes, or both conditions in São Paulo, Brazil (n=880) and Lima, Peru (n=432). Clinical effectiveness will be measured by reduction in depressive symptoms and gains in health-related quality of life. We will conduct cost-effectiveness and cost-utility analyses, providing estimates of the cost per at least 50% reduction in 9-item Patient Health Questionnaire scores, and cost per quality-adjusted life year gained. The measurement of clinical effectiveness and resource use will take place over baseline, 3-month follow-up, and 6-month follow-up in the intervention and control groups. We will use a mixed costing methodology (ie, a combination of top–down and bottom–up approaches) considering 4 cost categories: intervention (CONEMO related) costs, health care costs, patient and family costs, and productivity costs. We will collect unit costs from the RCTs and national administrative databases. The multinational economic evaluations will be fully split analyses with a multicountry costing approach. We will calculate incremental cost-effectiveness ratios and present 95% CIs from nonparametric bootstrapping (1000 replicates). We will perform deterministic and probabilistic sensitivity analyses. Finally, we will present cost-effectiveness acceptability curves to compare a range of possible cost-effectiveness thresholds.

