### Choice of Health Outcomes and Measurement of Effectiveness

Table 1 summarizes the health outcome measures and time of collection for the outcomes that will be used in the economic evaluations.

Two health outcomes will be measured: reduction in symptoms of depression and health-related quality of life. First, the primary outcome of effectiveness for the cost-effectiveness analysis will be the proportion of patients with at least 50% reduction in PHQ-9 scores. This indicator has been used in many depression trials and is considered a robust way of symptom improvement [22].

Second, the EuroQol 5-dimensional questionnaire, 3-level version (EQ-5D-3L) will be used to measure health-related quality of life and provide utilities for estimation of quality-adjusted life years (QALYs). The EQ-5D-3L is a generic preference-based measure used in many clinical trials for a wide range of health conditions and treatments [23].

The measurement of clinical effectiveness will take place over 3 periods: baseline, 3-month follow-up, and 6-month follow-up. Both countries used the same measures (PHQ-9 and EQ-5D-3L).

**Table 1 table1:** Summary of health outcomes measured.

Health outcomes	Measures	Timing of collection	Source of data
Depressive symptoms	PHQ-9^a^	Baseline, 3-month follow-up, and 6-month follow-up	Trials’ patient-reported outcomes
Quality of life	EQ-5D-3L^b^	Baseline, 3-month follow-up, and 6-month follow-up	Trials’ patient-reported outcomes

^a^PHQ-9: 9-item Patient Health Questionnaire.

^b^EQ-5D-3L: EuroQol 5-dimensional questionnaire, 3-level version.

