### Estimating Resources and Costs

The cost estimation will involve 3 stages: (1) identification of the costing items used to provide a particular service, (2) measurement of the resources used, (3) application of monetary value for each cost item, and calculation of the unit cost of a particular service [24].

The measurement of the resources will take place over 3 periods, baseline, 3-month follow-up, and 6-month follow-up, in the intervention and control groups. These are the same periods used to assess clinical effectiveness in the RCTs.

The measurement of resource use will be based on the group of patients from each country. The costing approach will apply unit cost estimates from Brazil and Peru to account for resource use in each of those countries.

Costs will be applied to the resources based on the unit costs or price weights most recently published in the respective official government databases (Department of Informatics of the National Health System, Departamento de Informática do Sistema Único de Saúde [DATASUS] in Brazil; and the Integral Health Insurance/Seguro Integral de Salud [SIS] in Peru). Other resource use not recorded in DATASUS or SIS will be based on LATIN-MH databases. These costs will be obtained in Brazilian reals (R$) and Peruvian sols (S$), as per rates in 2017. All costs will be adjusted for inflation using the Brazilian and Peruvian consumer price indexes for the current reference year (2021) and will be converted into international dollars (INT$) using the 2021 purchasing power parity (PPP) conversion factors for Brazil and Peru.

We will use a mixed costing methodology (ie, a combination of top–down and bottom–up approaches) considering 4 cost categories: intervention (CONEMO related) costs, health care costs, patient and family costs, and productivity costs. Table 2 presents an overview of resource use and cost measures that will be used in the economic evaluations. These include costs hypothesized to differ between CONEMO plus enhanced usual care (the intervention group) and enhanced usual care (the control group).

**Table 2 table2:** Summary of cost categories measured.

Cost category and unit					Unit cost		Source of data	

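### The ICER is defined from plain differences in arm means with no baseline covariate, although EQ-5D-3L and resource use are collected at baseline; adjustment would gain precision without new data

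*Protocol article*

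**What the plan says.** The estimator is in the protocol article under Analytic Methods: "Incremental cost-effectiveness ratios (ICERs) will be calculated as the arithmetic mean difference in cost between CONEMO plus enhanced usual care and enhanced usual care". The denominator is defined in the same way, the cost figure being "divided by the arithmetic mean difference in effect". Uncertainty comes from a nonparametric bootstrap with "random resamples for every 1000 pairs of outcomes and costs for the intervention and comparator groups to derive 95% CIs". Neither that section nor any other names a covariate or a regression step. The Sensitivity Analyses section varies resource quantities, unit costs and QALYs one at a time and does not mention baseline differences.

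Baseline data exist for both sides of the ratio. For outcomes (PHQ-9 and EQ-5D-3L): "The measurement of clinical effectiveness will take place over 3 periods: baseline, 3-month follow-up, and 6-month follow-up". For resource use: "The measurement of the resources will take place over 3 periods, baseline, 3-month follow-up, and 6-month follow-up, in the intervention and control groups". No section gives the baseline resource-use measurement a role in the analysis.

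On QALYs, the section on choice of health outcomes says only that EQ-5D-3L will "provide utilities for estimation of quality-adjusted life years (QALYs". The rule that turns three utility readings into a QALY is not given.

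**The concern.** Utility at baseline usually predicts utility at follow-up. If the QALY is the area under the utility curve from baseline, baseline utility is also one of its components. A raw difference in mean QALYs then carries whatever baseline utility difference randomisation happened to produce, and its standard error includes variation that a covariate already in the data set would explain.

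The horizon is at most 6 months, so the QALY difference is likely to be small. It is the denominator of the cost-utility ICER and feeds the acceptability curves. The two countries are analysed as fully split, so Peru (432 participants) cannot borrow precision from Brazil (880). The Discussion ties a favourable ICER to a case for scale-up, so avoidable imprecision in that denominator matters.

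**Working it through.** The document gives no SD, correlation or power figure for costs or QALYs, so there is no stated figure to reproduce. The check asks how much adjustment would gain under declared assumptions.

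**Inputs**
- From the document: 880 participants in Brazil and 432 in Peru; utilities at 0, 3 and 6 months; thresholds of $PPP3210 to 10,122 (Brazil) and $PPP1969 to 7747 (Peru) per QALY.
- Assumed: equal arms (440 and 216 per arm); the same utility SD at each visit, 0.20 (range 0.15 to 0.30); correlation of baseline with each follow-up a = 0.5 (0.3 to 0.6); correlation between the two follow-ups b = 0.6 (0.5 to 0.7); QALY as area under the curve.

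**Formulae.** QALY = 0.125·U0 + 0.25·U3 + 0.125·U6. In units of the utility variance:
- QALY variance V = 0.09375 + 2(0.03125a + 0.015625a + 0.03125b)
- Slope of QALY on U0: s = 0.125 + 0.375a
- Share of QALY variance removed by adjusting for U0: R² = s²/V
- Unadjusted-to-adjusted interval width for the QALY difference: 1/√(1 − R²)

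| a / b | V | s | R² | Width ratio |
|---|---|---|---|---|
| 0.3 / 0.5 | 0.153125 | 0.2375 | 0.37 | 1.26 |
| 0.5 / 0.6 | 0.178125 | 0.3125 | 0.55 | 1.49 |
| 0.6 / 0.7 | 0.19375 | 0.35 | 0.63 | 1.65 |

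These shares do not depend on the utility SD. With one common correlation of 0.3, 0.5 or 0.7 between all visits, R² is 0.40, 0.57 or 0.74. A simulation (216 per arm, SD 0.20, correlation 0.5, 5000 replicates) gave an adjusted-to-unadjusted SE ratio of 0.66. The dependence of the estimate on the baseline difference fell from a slope of 0.32 to about 0.01.

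**Baseline given no weight in the QALY** (0.25·U3 + 0.125·U6). At 0.5/0.6, V = 0.078125 + 0.0625 × 0.6 = 0.115625, s = 0.375 × 0.5 = 0.1875, and R² = 0.03516/0.115625 = 0.30. At 0.3/0.5 it is 0.01266/0.109375 = 0.12; at 0.6/0.7 it is 0.05063/0.121875 = 0.42.

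**Absolute size at SD 0.20, correlations 0.5/0.6.** The SE of the baseline utility difference is 0.20 × √(2/440) = 0.0135 in Brazil and 0.20 × √(2/216) = 0.0192 in Peru. A one-SE imbalance moves the raw QALY difference by 0.3125 times that: 0.0042 and 0.0060. Both scale with the SD: 0.0032 to 0.0063 (Brazil) and 0.0045 to 0.0090 (Peru) for SD 0.15 to 0.30. The QALY SD is 0.20 × √0.178125 = 0.0844, so the SE of the QALY difference is 0.0057 in Brazil and 0.0081 in Peru. Multiplying by √(1 − 0.548) = 0.672 gives adjusted SEs of 0.0038 and 0.0055.

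The shift is part of the unadjusted SE, not an addition to it: for Brazil, 0.0042² + 0.0038² ≈ 0.0057².

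For scale, a 1.96-SE imbalance valued at the document's thresholds is about $PPP27 to 84 per patient in Brazil and $PPP23 to 91 in Peru.

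**Costs.** Adjusting for baseline-period cost removes a share equal to the squared correlation between baseline and follow-up cost. The document does not give it. For illustration, 0.3 gives 9% and 0.5 gives 25%.

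**The case against.** The strongest reply is that the text never says the comparison is unadjusted. In cost analysis, specifying arithmetic means often serves to exclude medians and log-scale means, and a regression-adjusted increment is still a difference in arithmetic means. A journal article condenses its source, and a fuller analysis plan, not shown, may name covariates. This stands as far as it goes: a reader might infer that the plan rules adjustment out, and the document does not support that. But the article does state an estimator and a matching resampling scheme, and read as written they give a raw contrast between arms. That is a stated choice that can be improved, and not merely a detail left out.

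Second, the area-under-the-curve rule is an inference. That also stands. Without baseline in the QALY the gain is smaller, but it does not vanish.

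Third, the raw difference is unbiased under randomisation, and chance imbalance is sampling variation that the bootstrap interval already covers. This is right. A reader might infer that the ICER is systematically biased, or that imbalance and wide intervals are two separate harms. Neither follows; they are largely one loss of precision.

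Three further inferences go too far:
- That baseline resource use will be added to within-trial cost. No section says so, and the Health Care Costs section ties medicines to the study period.
- That the PHQ-9 outcome has the same defect. Response is a reduction of at least 50% in the participant's PHQ-9 score and so is already relative to baseline.
- That the shift is a known share of the expected QALY gain. The document gives no expected gain.

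**Conclusion.** The concern holds as a matter of efficiency. As written, the ICER rests on plain mean differences with no baseline covariate, while baseline utility and baseline resource use are available. Over 6 months, adjusting for baseline utility would remove about 37% to 63% of the QALY variance at baseline-to-follow-up correlations of 0.3 to 0.6, given equal arms, equal utility SDs and area-under-the-curve QALYs. With no baseline weight in the QALY the figure is about 30% at correlations 0.5/0.6 (12% to 42% over the range). None of these assumptions is stated in the document. The precision gain is clear in direction throughout, and its size depends on the correlations. For costs the direction is the same, but the size is unknown and may be modest. The point does not show bias, and it does not show that the authors have excluded adjustment.

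**What to change.** Amend the Analytic Methods text, or the analysis plan if one exists, as follows:

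1. State the QALY rule, including whether baseline utility carries weight.
2. Estimate incremental QALYs by regression on arm and baseline utility, separately in each country.
3. Estimate incremental costs by regression on arm and baseline-period cost, and say that baseline-period resource use enters only as a covariate.
4. Resample participants with their costs and outcomes kept together, and refit both models in every bootstrap replicate so that the cost-outcome correlation is preserved. Seemingly unrelated regression is one acceptable way to do this; separate regressions refitted in the same replicate are another.
5. Form the ICER, its interval and the acceptability curves from the adjusted differences, and report the unadjusted differences alongside.

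Adjusting the response outcome for baseline PHQ-9 is optional. The change costs a few sentences and minor code, and needs no new data. It should be fixed before results by arm are examined, so that the choice of covariates cannot be led by them.
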